Functional tasks that reflect daily movements, such as the sit-to-stand task, could be used to monitor knee ROM. These tasks are easier to complete in the home environment than goniometer measurements and represent functional ability. The sit-to-stand test is recommended for monitoring recovery from TKR surgery [10]. Evidence suggests that sagittal plane knee ROM is decreased during the sit-to-stand task after TKR surgery compared to healthy controls [11], indicating that this task may be used to measure ROM in post-operative patients. Therefore, this study will use the sit-to-stand test to measure ROM in a home-based setting.

The computer vision-based approach offers a non-invasive, objective method to monitor knee flexion in patients with knee stiffness, which could inform treatment decisions to improve outcomes. Currently, no tool exists to remotely and accurately detect early post-surgical knee stiffness. This study seeks to develop a cost-effective tool for measuring and quantifying knee stiffness pre- and post-TKR surgery for use across the NHS. This study also aims to determine its reliability, feasibility, and usability for implementation in the home.

The primary objectives of the study are the following:To provide proof of concept for a computer vision-based approach that measures knee ROM for use in the home setting.To validate the computer vision-based approach in people who have undergone TKR by ascertaining the test–retest reliability of algorithm outputs such as knee flexion/extension angles.To investigate the integration of the computer vision-based approach into clinical practice through focus groups and identify key development areas for successful implementation.

The secondary objectives of the study are the following:To explore how pain influences knee ROM in people who undergone TKR.To investigate the relationship between muscle activation and ROM in people who have undergone TKR and in healthy controls.To describe the association between physical activity and ROM in people who have undergone TKR.To identify the potential risk factors, measured using questionnaires, linked with knee stiffness post-TKR surgery.

This study will be split into three stages: (1) focus groups, (2) validation of the computer vision-based approach for measuring knee range of motion in the laboratory, and (3) home testing. These will be outlined and addressed separately within the protocol.

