#### Data Analysis 

Descriptive and frequency statistics will be reported for demographic, usability, acceptability, and feasibility data, and missing data will be reported.

To validate the motion capture measurements of the computer vision-based motion capture software against those from the marker-based motion capture software, we will use Bland–Altman (Tukey mean-difference) plots to assess for systematic deviation and determine any necessary bias correction.

To determine the test–retest reliability of the motion capture knee ROM measurements and to identify potential risk factors associated with knee stiffness, we will apply mixed-effects linear models for knee ROM adjusted for the group (group that underwent TKR or control) and questionnaire scores, with random effects for each participant. Variance components of the mixed-effects model may be used to estimate reliability measures as follows:

Relative reliability will be estimated using the intra-class correlation (2) (ICC) of Two-Way Random Effects [24]. Interpretation of ICC values will be conducted according to published guidance: an ICC of less than 0.5 is considered poor, between 0.5 and 0.75 is moderate, between 0.75 and 0.90 is good, and above 0.90 is excellent [25]. Absolute reliability will be estimated by the standard error of measurement (SEM) [26], calculated as $SD\left(standard\;deviation\right)\times \surd (1-ICC)$. The Minimal Detectable Change at the 95% confidence level (${MDC}_{95}$) is the minimal amount of change that would be accepted as a real change greater than that seen due to random variation or error [26]. MDC_95_ is calculated as follows: ${MDC}_{95}=1.96\times SEM\times \sqrt{2}$.

To explore the relationship between knee ROM and pain, muscle activation, physical activity, and potential risk factors, appropriate correlations/statistical tests will be selected to describe associations.

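### Test–retest reliability comes from a model adjusted for questionnaire scores and pooled over both groups, which biases the ICC low if the scores predict ROM and gives no TKR-specific estimate

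*Protocol article*

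**What the plan says.** The second primary objective in the Introduction is "To validate the computer vision-based approach in people who have undergone TKR by ascertaining the test–retest reliability" of outputs such as knee angles. The target population is therefore TKR patients.

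The Data Analysis part of section 4.2 names one model specification for that purpose "and to identify potential risk factors associated with knee stiffness". It reads "we will apply mixed-effects linear models for knee ROM adjusted for the group (group that underwent TKR or control) and questionnaire scores". The only random part that it describes is at participant level. It then says "Variance components of the mixed-effects model may be used to estimate reliability measures as follows", and lists three measures:

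- The ICC: "Relative reliability will be estimated using the intra-class correlation (2) (ICC) of Two-Way Random Effects", read against bands at 0.5, 0.75 and 0.90.
- SEM = SD × √(1 − ICC), without saying which SD.
- MDC95 = 1.96 × SEM × √2.

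Section 4.3 uses MDC95 to judge whether home ROM agrees with laboratory ROM. No model without questionnaire scores, no TKR-only fit and no group-specific variance is described.

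**The concern.** Reliability and risk-factor analysis need different models. The ICC is the share of total variance that lies between participants. A risk-factor model tries to explain exactly that variance. The article expects some scores to be related to stiffness, since it looks for risk factors among the questionnaires. To the extent that it succeeds, an ICC from the same model falls although the software measures no worse.

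Three further features of the text bear on the same outputs. The undefined SD allows an unadjusted SD to be combined with an adjusted ICC. The pooled fit has one residual variance for patients and controls. Random effects described for participants alone form a one-way model, whereas the named ICC is two-way.

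The ICC and MDC95 are outputs of a primary objective, and MDC95 is also the yardstick for home testing. An MDC95 that is too large would make home recordings look compatible too easily; one that is too small would do the reverse.

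**Working it through.** The article gives no expected ICC, SEM, SD or variance component, so there is no figure of its own to reproduce on this point. (Its only computed figures, the powers in Table 1, do reproduce with a two-sided t test and 30 per group, but they do not bear on reliability.) All variances below are assumptions chosen to show direction and size.

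**1. Adjustment for questionnaire scores.** Assume total SD 10° and true ICC 0.90, so between-participant variance is 90 and within-participant variance 10. Let R² be the share of between-participant variance explained by the scores. Then

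ICC = 90(1 − R²) / [90(1 − R²) + 10].

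The SD from the same model is √[90(1 − R²) + 10]; the unadjusted SD stays at 10°.

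| R² | ICC | SD, same model | SEM / MDC95, same-model SD | SEM / MDC95, unadjusted SD |
|---|---|---|---|---|
| 0 | 0.90 | 10.0° | 3.2° / 8.8° | 3.2° / 8.8° |
| 20% | 72/82 = 0.88 | 9.1° | 3.2° / 8.8° | 3.5° / 9.7° |
| 40% | 54/64 = 0.84 | 8.0° | 3.2° / 8.8° | 4.0° / 11.0° |
| 60% | 36/46 = 0.78 | 6.8° | 3.2° / 8.8° | 4.7° / 12.9° |

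The ICC falls in every row. SEM and MDC95 do not move if the SD comes from the same model, because SD × √(1 − ICC) then returns the residual SD, √10 = 3.2°. With the unadjusted SD they rise by 10, 25 and 47%.

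The band can change. With between-participant SD 10° and within-participant SD 4°, the true ICC is 100/116 = 0.862. At R² = 70% it is 30/46 = 0.652, so good becomes moderate.

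**2. One residual variance for both groups.** With equal group sizes, pooled SEM = √[(SEM²TKR + SEM²control)/2].

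- 4° and 4°: pooled 4.0°, no bias.
- 5° in TKR and 3° in controls: √17 = 4.12°, MDC95 11.4° against 13.9° for TKR, 18% too small.
- 3° in TKR and 5° in controls: MDC95 11.4° against 8.3°, 37% too large.

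**3. Participant random effect without a trial effect.** Simulated with 60 participants, 3 repeats, between-participant SD 10° and residual SD 4°. For trial SDs of 0, 1, 2 and 4°, the mean ICC(1) is 0.858, 0.850, 0.828 and 0.750. The mean ICC(2,1) is 0.858, 0.850, 0.831 and 0.763. The largest difference is 0.013, because in a one-way model the trial variance goes into the residual.

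**4. The features together.** Simulated with 30 + 30 participants, 3 repeats, between-participant SD 10°, within-participant SD 5° in TKR and 3° in controls, a 10° group gap, and a score explaining about 49% of between-participant variance.

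- Model as described: ICC 0.74, residual SEM 4.1°, MDC95 11.3°.
- Same ICC with the unadjusted pooled SD: SEM 5.9°, MDC95 16.2°.
- TKR patients only, no scores: ICC 0.80, SEM 4.9°, MDC95 13.7°.

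One description thus allows an MDC95 below or above the TKR value, depending on how the SD is read.

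**The case against.** A reader might infer that ICC, SEM and MDC95 will all be wrong for TKR patients. The document does not support that. Participant-level scores leave the residual variance alone, so SEM and MDC95 survive the adjustment when SD and ICC come from one model, and the text does not say that they will not. Nothing in the article shows that controls are steadier than patients, so a bias from pooling is possible but not established, and its direction is unknown.

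Other points for the plan are fair. Using the variance components is put as a possibility, and the text speaks of models in the plural. The section closes with separate association analyses that include risk factors. Adjusting for group is helpful: with a 20° gap between group means (between-participant SD 10°, within-participant SD 4°), the ICC would be 200/216 = 0.926 without it and 100/116 = 0.862 with it. The text does not say that participant is the only random effect, and naming a two-way ICC may mean that the model sentence is abbreviated. The study is a pilot, and the ICC bands are descriptive rather than pass/fail limits.

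Most of this limits the size of the point and does not remove it. The plural models share one stated specification, which includes the questionnaire scores and is introduced for reliability by name. No other reliability model is given. The closing association analyses only show that the scores are not needed in the reliability model.

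**Conclusion.** The point holds for the ICC. Followed as written, the model gives an ICC conditional on the questionnaire scores, biased low to the extent that the scores predict ROM and then read against bands that do not allow for this. Under an assumed true ICC of 0.90 the loss is 0.02, 0.06 or 0.12 at R² of 20, 40 or 60%; if the scores explain nothing, there is no loss.

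For SEM and MDC95 the risk is conditional: inflation if an unadjusted SD enters the formula, and misstatement for TKR patients, either way, if within-participant error differs between groups. The lack of a TKR-specific estimate is nevertheless a mismatch with the stated objective. The one-way versus two-way inconsistency should be corrected for coherence, but is worth only about 0.01 in the ICC. Every size given here rests on assumed variances.

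**What to change.** Separate the two purposes in the analysis text.

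1. **Reliability.** Fit knee ROM with random effects for participant and trial and no questionnaire scores. Fit it in the TKR group as the primary estimate and in controls separately, or jointly with group-specific variances. Compute ICC(2,1) from those components. Take SEM directly as the square root of the trial-plus-residual variance, which removes the question of which SD to use, and derive MDC95 for section 4.3 from the TKR estimate.
2. **Risk factors.** Keep the model adjusted for group and questionnaire scores for associations only.

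No new data are needed. The cost is one extra model and some precision. With three repeats and roughly normal errors, the relative standard error of an SEM is about 1/√(2 × degrees of freedom). For 30 patients that is 1/√(2 × 60) = 9%; for 60 participants pooled it is 1/√(2 × 120) = 6.5%. That is a modest price for an estimate in the population that the objective names.

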### 4.3. Home Testing

Participants will be asked to set up a camera device (mobile phone/tablet) in their homes and record themselves completing the following:The sit-to-stand test;If possible (within the limitations of the participants’ available space and ability to capture the trial), the TUG walk.

The research team will send the participants an email that will allow them to upload their video files to REDCAP. Videos will be analysed using a custom computer vision-based application. Participants will be asked to complete a System Usability Scale questionnaire [27,28]. The participants will be asked to complete this task within a week of the lab visit.

Descriptive and frequency statistics will be reported for the System Usability Scale questionnaire, and missing data will be reported. Knee ROM will be compared to the $MDC_{95}$ to determine compatibility with lab-based measurements.

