## Abstract

Pain and knee stiffness are common problems following total knee replacement surgery, with 10–20% of patients reporting dissatisfaction following their procedure. A remote assessment of knee stiffness could improve outcomes through continuous monitoring, facilitating timely intervention. Using machine learning algorithms, computer vision can extract joint angles from video footage, offering a method to monitor knee range of motion in patients’ homes. This study outlines a protocol to provide proof of concept and validate a computer vision-based approach for measuring knee range of motion in individuals who have undergone total knee replacement. The study also explores the feasibility of integrating this technology into clinical practice, enhancing post-operative care. The study is divided into three components: carrying out focus groups, validating the computer vision-based software, and home testing. The focus groups will involve five people who underwent total knee replacement and ten healthcare professionals or carers who will discuss the deployment of the software in clinical settings. For the validation phase, 60 participants, including 30 patients who underwent total knee replacement surgery five to nine weeks prior and 30 healthy controls, will be recruited. The participants will perform five tasks, including the sit-to-stand test, where knee range of motion will be measured using computer vision-based markerless motion capture software, marker-based motion capture, and physiotherapy assessments. The accuracy and reliability of the software will be evaluated against these established methods. Participants will perform the sit-to-stand task at home. This will allow for a comparison between home-recorded and lab-based data. The findings from this study have the potential to significantly enhance the monitoring of knee stiffness following total knee replacement. By providing accurate, remote measurements and enabling the early detection of issues, this technology could facilitate timely referrals to non-surgical treatments, ultimately reducing the need for costly and invasive procedures to improve knee range of motion.

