### 2.3. Home Testing

Participants recruited for the computer vision-based approach validation will then undertake the home testing procedure. The home testing protocol will take place in the participants’ own homes.

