### 4.2. Validation of Computer Vision-Based Approach

Participants will wear an activity monitoring accelerometer for one week before the experimental session at the university. The accelerometer will be removed at the session. Physical activity monitoring can be repeated in the week following the visit if there are any problems with the data.

Motion capture markers and sEMG electrodes will then be applied. A physiotherapist will administer questionnaires.

A static trial will be recorded, followed by a series of gait/functional tasks. Participants will complete a two-minute walk on a treadmill at a self-selected walking speed. A sit-to-stand test will then be completed three times: participants will start in a seated position and stand up, then sit down without the use of their hands.

Participants will then be asked to complete the timed-up-and-go test (TUG) three times. The participant will start by sitting down in a chair and will stand up, walk forward three metres, turn around a cone, and then walk back to the chair before sitting down. Finally, an overground walking task will be completed three times: the participant will be asked to walk five metres, turn around a cone, and walk another five metres.

Knee range of motion will be measured by a trained physiotherapist. The maximum and minimum angles will be measured using a universal goniometer whilst lying on a physiotherapy couch and whilst seated on a chair.

Participants will be offered the chance to rest between procedures for as long as preferred. The Single Ease Question (SEQ) is a concise post-task questionnaire utilising a seven-point rating scale to gauge the perception of the difficulty or ease of a specific task. The SEQ will be completed after every task. Following the completion of testing, all equipment will be removed from the participant.

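### Home sit-to-stand ROM is judged against a same-session lab MDC95, with seat height and foot position neither matched nor recorded, so a home–lab difference cannot be attributed to any one source

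*Protocol article*

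**What the plan says.** **Lab (section 4.2).** The session opens with a static trial and a treadmill walk: "Participants will complete a two-minute walk on a treadmill at a self-selected walking speed". Then: "A sit-to-stand test will then be completed three times", with the instruction that "participants will start in a seated position and stand up, then sit down without the use of their hands". Free rest is allowed: "Participants will be offered the chance to rest between procedures for as long as preferred". No chair height or foot position is given.

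**Home (sections 2.3, 3.3 and 4.3).** "The home testing protocol will take place in the participants’ own homes". The instruction is "Participants will be asked to set up a camera device (mobile phone/tablet) in their homes and record themselves completing the following", namely the sit-to-stand and, where space allows, the timed-up-and-go. Participants use their own phone or tablet. On timing: "The participants will be asked to complete this task within a week of the lab visit". The videos go through an application described only as custom. The lab software is named as Digimotion 5.01 and Digimove 4.01, and the article does not say whether the home application is either of these.

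**How the two are compared.** The Abstract says of the home sit-to-stand: "This will allow for a comparison between home-recorded and lab-based data". Section 4.3 makes this concrete: home ROM is compared with the MDC95 to judge compatibility with the lab. The Data Analysis part of section 4.2 defines SEM as SD × √(1 − ICC) and MDC95 as 1.96 × SEM × √2, and treats MDC95 as the smallest change that counts as real rather than as random variation or error.

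**The concern.** Knee ROM in a sit-to-stand depends heavily on the set-up. The knee starts at the flexion that the seat and feet impose and finishes near extension. A lower seat or feet drawn further back gives a larger ROM in the same knee, measured without error.

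The only repeat measurements described are the trials within one lab visit. An MDC95 built from them contains no change of chair, no change of day and no change of recording device. All three change between lab and home. The TKR knees were operated on five to nine weeks before and may still be improving during the interval of up to a week.

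By the plan's own definition, anything beyond the MDC95 is real change. A different chair produces exactly that, and the rule in section 4.3 would report it as incompatibility. In the other direction, a chair effect could offset a device or camera effect and make the two settings look compatible. The home–lab comparison is the only ROM evidence from the home that the article describes, so its reading matters for the first primary objective (proof of concept for home use).

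**Working it through.** The article gives no SD, ICC, segment lengths or expected home–lab difference. Its one computed figure, the power in Table 1, reproduces (two-sided two-sample t-test, 30 per group) but has no bearing here. What follows illustrates size under stated assumptions.

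**1. Effect of set-up on seated knee flexion.** Assumed: height 165 cm, thigh 40.4 cm, shank 40.6 cm, thigh near horizontal and shank near vertical at the start.
- Seat 5 cm lower or higher: arcsin(5 / 40.4) = 7.1°.
- Feet 10 cm further back: arcsin(10 / 40.6) = 14.3°. Foot position is not fixed in the lab either, so part of this variation may already be in the lab repeat trials.

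**2. MDC95 by the plan's formulas**, with an assumed SD of 10°:

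| ICC | SEM = 10 × √(1 − ICC) | MDC95 = 1.96 × SEM × √2 |
|---|---|---|
| 0.95 | 2.24° | 6.2° |
| 0.90 | 3.16° | 8.8° |
| 0.75 | 5.00° | 13.9° |

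A 7.1° shift equals the MDC95 when SEM = 7.1 / (1.96 × √2) = 2.56°, that is 1 − ICC = (2.56 / 10)² = 0.066, or ICC about 0.93. Above that, a 5 cm seat difference alone exceeds the MDC95; below it, it does not.

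**3. Share of participants beyond the MDC95 with measurement error unchanged.** Take the home–lab difference as Normal with mean b and variance 2·SEM² + c², where b is a mean shift from home conditions and c their between-participant SD.
- b = 0, c = 0: 5.0%.
- b = 7.1°, c = 0: b / SEM is 3.18, 2.25 and 1.42 at ICC 0.95, 0.90 and 0.75. The upper limit standardises to (2.77 − b / SEM) / √2 = −0.29, 0.37 and 0.95, so about 61%, 36% and 17% exceed.
- b = 0, with home conditions varying between participants: 11.0% exceed at c = 1 SEM and 25.8% at c = 2 SEM. At ICC 0.90, 2 SEM is 6.3°, a little less than the effect of 5 cm of seat height.

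**4. Can the source be identified?** In this model b may come from the chair, from recovery, from the device or camera, or from the software. The same b gives the same percentages whatever its origin. With no marker-based or goniometer measurement at home and no record of seat height, nothing in the described data separates them.

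**The case against.** **The article condenses a fuller protocol.** Seating instructions may be there, or in the patient materials that section 2.1 says will come out of the focus groups. This has some weight: the own chair is an inference from the home setting and is not stated. But those materials are not said to cover seating. The interval and the MDC95 criterion are stated rules, not omissions.

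**Ordinary, unstandardised use is what a home study is for.** That is fair, and it is a reason not to force identical conditions. It is also a reason not to use a same-session lab threshold as the yardstick. Seat height still has to be recorded if a discrepancy is to be interpreted.

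**The software is validated in the lab.** It is, by Bland–Altman analysis against marker-based capture, and this point does not touch that. A constant software bias would also largely cancel in a home–lab difference if the same software is used in both places.

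**The other ingredients are weak.** The treadmill walk is two minutes at a self-selected speed with free rest afterwards, so it is not a persuasive source of difference. Recovery over a week has no size in the article.

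Two stronger readings are tempting. One is that a home–lab difference reflects the chair and not the software. The documents do not support this, because the device, the camera position and possibly the application also differ. The other is that the home stage cannot answer the first primary objective at all. That does not follow either: whether recordings are made, uploaded and analysable, and the System Usability Scale results, also bear on proof of concept.

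**Conclusion.** The point holds in a limited form. The home–lab comparison confounds task conditions, true change, recording set-up and software error, and a same-session MDC95 covers only part of that variation. What is weakened is the home–lab agreement part of the first primary objective.

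The size is material but rests on assumptions. If every participant's seat differed by 5 cm in the same direction, between about 17% and 61% would fall beyond the MDC95 with measurement error unchanged, against 5% otherwise (ICC 0.75 to 0.95, SD 10°, segment lengths as assumed). The direction of the argument does not depend on these values. It is worth settling before recruitment, because seat height cannot be reliably recovered afterwards.

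**What to change.** In sections 4.2 and 4.3:
- Record seat height for the sit-to-stand in the lab and at home. Where practical, set the lab seat to the home height.
- Give the same foot-placement and no-hands instruction in both places.
- Record the number of days between the lab visit and the home recording.
- Report the home–lab ROM difference adjusted for the seat-height difference and the interval. State that exceeding the same-session MDC95 is not, on its own, evidence that the software is incompatible.

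The cost is one extra measurement by the participant and two covariates in the comparison. Matching the lab seat, where it is done, makes lab seat height vary between participants. The adjustment removes the chair and timing components as far as they are measured. Device, camera and software remain pooled, and the report should say so. The lab task order and the one-week window can stay as they are.

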#### 3.2.3. Motion Capture

Each participant will be provided with a tight-fitting t-shirt and gym shorts. A full-body set of retroreflective markers (*n* = 60) based on the conventional gait model 2 [22] will be applied to the participant using surgical tape. Marker-based motion capture data will be collected using 12 Vicon Valkyrie VK16 cameras (Vicon, Oxford, UK). Data will be recorded at 100 Hz. Motion capture data will be processed in Vicon Nexus software (version 2.16) and analysed in Visual3D (C-Motion, Rockville, MD, USA).

Computer vision-based markerless motion capture will be run on two laptops to capture data: in the sagittal plane and at a 30° angle. Digimotion software (version 5.01) will be run locally on each laptop to activate the webcam and calculate hip, knee, and ankle angles in real time. Data will be recorded at 30 Hz. Two video cameras and three iPads/iPhones (Apple, Cupertino, CA, USA) will record videos from different angles to determine any angle effect. Digimove software (version 4.01) will calculate hip, knee and ankle angles from recorded videos. Videos will be recorded at 30 Hz.

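### Home–lab compatibility is judged against an MDC95 computed from the study's own SEM, so the limit widens as the software gets noisier, and no home-minus-lab bias estimate is stated

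*Protocol article*

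**What the plan says.** Section 4.3 has participants film the sit-to-stand test at home, and the TUG where possible, on their own device. On timing: "The participants will be asked to complete this task within a week of the lab visit". On processing: "Videos will be analysed using a custom computer vision-based application". The only numerical home-versus-lab criterion is that knee ROM is compared with the MDC95 "to determine compatibility with lab-based measurements". The section does not say whether the comparison is per person or on the group mean, or what share of participants must fall inside.

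The Data Analysis section under 4.2 sets SEM = SD × √(1 − ICC) and MDC95 = 1.96 × SEM × √2. It explains that MDC95 "is the minimal amount of change that would be accepted as a real change greater than that seen due to random variation or error". ICC values are graded in four bands, but no minimum ICC is required before MDC95 may serve as the home–lab limit. For the software against marker-based capture, "we will use Bland–Altman (Tukey mean-difference) plots to assess for systematic deviation and determine any necessary bias correction". No such analysis is stated for home against lab.

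For lab recordings, section 3.2.3 says "Digimove software (version 4.01) will calculate hip, knee and ankle angles from recorded videos".

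**The concern.** On the article's own definition, a difference below MDC95 cannot be told apart from measurement error. That is not evidence that two settings agree. Used as an acceptance limit, MDC95 has two weaknesses.

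- **It scales with the error of the tool under test.** The same home–lab difference passes more easily when the software is less repeatable.
- **It mixes bias with noise.** A uniform shift at home and random scatter at home are measured against the same limit, and nothing stated estimates the shift.

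A shift is plausible from the text: participants set up their own devices, and TKR patients five to nine weeks after surgery may still be recovering during the gap of up to a week.

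The first primary objective is proof of concept for use in the home, and this is the only stated numerical test of home measurements. A noisy, biased home measure could be labelled compatible, and the size of any bias would not be reported.

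**Working it through.** **Inputs.** From the Data Analysis section: SEM = SD × √(1 − ICC) and MDC95 = 1.96 × √2 × SEM. From section 2.2.2: 60 participants, 40 with complete data. The article gives no SD, ICC or SEM for knee ROM, so SEMs of 2° to 5° and a 5° offset are assumptions for illustration. The plan states no figure on this point to reproduce.

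**Step 1: how the limit moves.** MDC95 = 2.77 × SEM, which is 5.5°, 8.3°, 11.1° and 13.9° at SEM 2°, 3°, 4° and 5°. In SD units it is 1.96 × √2 × √(1 − ICC), which is 0.62 at ICC 0.95 and 1.96 at ICC 0.50. At a given SD the limit is therefore about 3.2 times wider at the lower ICC (1.96 / 0.62).

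**Step 2: share of participants inside the limit.** Suppose home error equals lab error and home readings are shifted by b. The home–lab difference D is then normal with mean b and standard deviation s = √2 × SEM, and

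P(|D| ≤ MDC95) = Φ((MDC95 − b)/s) − Φ((−MDC95 − b)/s).

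At SEM 2° and b = 5°: s = 2.83°, so Φ(0.192) − Φ(−3.728) = 0.576.

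| SEM | MDC95 | Inside, b = 0° | Inside, b = 5° |
|---|---|---|---|
| 2° | 5.5° | 95% | 58% |
| 3° | 8.3° | 95% | 78% |
| 4° | 11.1° | 95% | 86% |
| 5° | 13.9° | 95% | 89% |

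The same offset moves the share inside by 37 points at SEM 2° (95 − 58) but by 6 points at SEM 5° (95 − 89).

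**Step 3: hold the home–lab difference fixed.** If D has mean 5° and SD 6° whatever the lab SEM (assumption), the shares inside are 50%, 70%, 84% and 93%. Identical home data receive a better result only because the lab SEM is larger.

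**Step 4: the opposite error.** Section 4.2 describes three sit-to-stand repeats within one lab visit. If SEM comes from these alone, it omits day-to-day and set-up variation. With SEM 2° (limit 5.5°) and a home–lab difference with mean 0° and SD 6° (assumption), only 64% fall inside, although there is no bias.

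**Step 5: what the paired data could give.** The 95% confidence interval for the mean home–lab difference has half-width of about 1.96 × √2 × SEM / √n. With n = 40 this is 0.9° at SEM 2° and 2.2° at SEM 5°. If the 40 split evenly by group (assumption), n = 20 gives 1.2° and 3.1°. An offset of 5° would be estimated clearly in each case.

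**The case against.** The strongest reply is that the comparison does respond to offsets. With no offset 95% fall inside, so 58% at SEM 2° is a plain signal. An illustrative one-sided check on 40 participants (35 or fewer inside, alpha 0.048) would flag the 5° offset with probability 1.00, 0.96, 0.70 and 0.45 at SEM 2°, 3°, 4° and 5°. This stands. A reader might infer that the rule cannot detect a systematic home offset at all, and the figures do not support that. But the article states no such check, and its sensitivity falls as the tool worsens.

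Second, asking whether an individual difference exceeds measurement error is an ordinary use of MDC95, and poor reliability would show in the graded ICC and the SEM. This also stands, but seeing that the tool is noisy does not change a verdict measured against a limit made from that noise. A reader might also infer that the plan would declare home use proven. It says only that ROM is compared with MDC95, and fixes no pass mark.

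Third, recovery, seating and device differences mostly enlarge the home–lab difference and make the limit harder to meet. Adding an assumed 4° of home-only SD lowers the shares inside at a 5° offset to 53%, 70%, 80% and 85%. The level drops, but the rise with SEM remains.

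Two further readings are tempting and unsupported. The generic description of the home application does not show that it differs from the named lab software; the article simply does not say that they are the same. And no cut-off for stiffness in degrees is given, so no rate of misclassified stiffness can be claimed.

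Finally, this is a pilot seeking proof of concept, and the raw readings will exist for a later analysis. That lowers the severity.

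**Conclusion.** The point holds in a limited form. The stated limit is proportional to the software's own error, does not separate home–lab bias from noise, and can label a mean offset smaller than MDC95 as compatible. No estimate of that bias is stated. In the illustration, the share inside MDC95 under a constant 5° offset rises from 58% to 89% as SEM goes from 2° to 5°. The percentages rest on assumed SEMs, normal differences, home error equal to lab error and a per-person reading of the comparison. The dependence on SEM follows from the formula alone. The error can also run the other way if SEM reflects only same-session repeats. In neither case is the limit tied to a tolerance chosen for its meaning in degrees. Severity: should-fix.

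**What to change.** Make the home–lab criterion a paired home-minus-lab Bland–Altman analysis, giving the mean difference with 95% CI and the 95% limits of agreement. Report it separately for controls and TKR patients, because the gap of up to a week may include recovery in the patients. Judge it against an agreement limit in degrees that the study team sets before data are seen, and keep MDC95 as a descriptive reliability figure only. State that home videos and lab phone or tablet videos are processed with the same software version. Recording home seat height at upload is optional.

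The cost is a short change of wording, one agreed limit and a little more analysis. No extra participants or visits are needed. The downside is that a fixed limit can be failed, and intervals by group are wider than for the pooled sample.
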